## Measures

### Survey

*
**Persons Served.**
* The survey will gather demographic information including age, gender, race/ethnicity, sexual orientation, educational level, language, immigration history/status, family characteristics (e.g., number of children), housing status, income, and religion and questions about their pathway to, and tenure in, MISSION-CJ and DTC (e.g., Who referred you?, How long have you been in the program?). Their perceptions of MISSION-CJ and DTC providers’ cultural competency will be measured by an adapted version of the Iowa Cultural Understanding Assessment–Client Form [42]. The Iowa Cultural Understanding Assessment–Client Form scale is a brief assessment for understanding organizational culture through the lens of client perspectives based on staff–client relations, environmental factors, and service delivery processes. This measure was selected because it quantitatively assesses aspects of HEIF’s three health equity domains which are important in understanding equitable implementation. The survey, offered in English and Spanish, will take 10–15 minutes, and can be completed online, by phone, or by pen/paper. The survey was written at a 6th grade reading level. Participants can opt to have the survey read to them by the interviewer and verbally respond to survey questions.

*
**Providers**.* The survey will provide information about the providers’ demographics including: gender, race/ethnicity, and educational level; organizational cultural competence assessment; and self-assessment of their own cultural competency. The organizational and self-assessment questions were adapted from the work of the Association of University Centers on Disabilities (AUCD) Multicultural Council’s Assessment of Organizational Cultural Competence, which [43] assists organizations in assessing their progress towards cultural competence, both at the organizational and individual level. The survey will take about 10–15 minutes to complete and can be completed online, by phone, or pen/paper.

### Interview

We will conduct semi-structured individual interviews with participants to identify perceived barriers and facilitators to MISSION-CJ implementation in Drug Court. The interview guide will be based on HEIF components and will specifically elicit perspectives on the following topics: needs of both persons served and providers/administrators in regard to COD treatment and its delivery for the target populations; current implementation of MISSION-CJ and DTC; multilevel factors that might facilitate or inhibit equitable implementation of MISSION; and ideas about how to address identified barriers. HEIF-informed semi-structured interview guides (see supplemental materials for sample interview questions by HEIF domain) will be developed using iterative community and provider feedback. Iterative drafts of the interview guide will be edited by the advisory board, study team, and an external qualitative researcher. Thirty interviews will be completed – 15 per group or until the data collected reaches saturation. Sample sizes of 10–15 [44] per group have been found to meet the threshold for data saturation in qualitative research [45].

Analytic Plan: Once data are collected, cleaned, and entered in respective software for management (SPSS for quantitative data from surveys, Dedoose for qualitative data from semi-structured interviews), each data type (qualitative data from interviews and quantitative data from surveys) will be analyzed independently and then merged and presented to the study team to integrate quantitative and qualitative findings. Directed content analysis [46] will be used for qualitative data to categorize according to domains from the HEIF. Coding will be completed by the study team – the PI (coder A), two doctoral level coders (coders B and C), and one bachelor’s in psychology level coder (coder D). Coders will extract data on specific concepts related to implementation, disparities, culture, cultural identities, and equity (see Table 3 for coding definitions) and barriers or facilitators of MISSION-CJ implementation. Quantitative survey data will be analyzed, and descriptive statistics will be generated. Mean responses to survey items will be compared by groups (e.g., drug court sites, provider roles, gender, race, ethnicity, etc.) to determine differences between specific groups (e.g., persons served ratings on program cultural competency vs. providers/administrators’ ratings of program cultural competency).

**Table 3. tbl3:** Coding definition

Coding	Coding Definition
Implementation	A specified set of activities, methods, and strategies designed and used to put into practice a practices or program.
Disparity	Experiences, perceptions, or reasons for unjust differences in treatment.
Culture	Shared characteristics of a group of people that structures the way people view the world. Set of beliefs, norms, and values that influence ideas about the nature of relationships, the way people live their lives, and the way people organize their world.
Cultural identities	Includes age, developmental disabilities, acquired disabilities, religion, ethnicity, sexual orientation, socioeconomic status, indigenous group membership, nationality, gender, gender identity, and gender expression, and veteran status. This broad definition allows for exploration of multiple intersecting cultural identities.
Equity	Equity is an ongoing process of assessing needs, acknowledging and correcting historical inequities, addressing social determinants (e.g., employment and housing stability, insurance status, proximity to services, and culturally responsive care), and creating conditions for optimal outcomes by members of all cultural identity groups.

The qualitative data will be quantified. For example, presenting ever-coded (e.g., the number of transcripts that had the code assigned ever) and frequency (e.g., the number of times the code was assigned throughout all transcripts) counts will provide additional data to support salience of emergent themes. We will use a joint display to merge the two data types by illustratively bringing them together to complement understanding and interpretation by detailing codes, themes, and survey responses to engage in a side-by-side comparison. This strategy has been used in prior studies to identify points of convergence and divergence in participant responses [47] and provides a more complete, unified explanation than either single data type alone.

### 
Aim 2: Identify and Prioritize Actionable Implementation Strategies to Address Barriers to Equitable MISSION-CJ Implementation in DTCs Using Concept Mapping with 60 Black/African American and/or Hispanic/Latino Persons Served by MISSION-CJ in DTCs and Related Providers/Administrators

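### The example comparison of persons-served and provider mean ratings of program cultural competency sets two different instruments against each other, so a difference in means cannot be read as a perception gap

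*Protocol article*

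**What the plan says.** All places are in the protocol article.

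- **Aim 1 analytic plan (under Interview).** The quantitative step reads "Mean responses to survey items will be compared by groups". Several grouping factors are listed (court site, provider role, gender, race, ethnicity), and the stated purpose is to find differences between groups. The worked example in parentheses is "persons served ratings on program cultural competency vs. providers/administrators’ ratings of program cultural competency".
- **Survey, persons served.** "Their perceptions of MISSION-CJ and DTC providers’ cultural competency" "will be measured by an adapted version of the Iowa Cultural Understanding Assessment–Client Form". The form is described as a "brief assessment for understanding organizational culture through the lens of client perspectives based on staff–client relations, environmental factors, and service delivery processes".
- **Survey, providers.** Besides demographics, the content is "organizational cultural competence assessment; and self-assessment of their own cultural competency". On the source: "The organizational and self-assessment questions were adapted from the work of the Association of University Centers on Disabilities".
- **Table 1 and Aim 1 participants.** There are 15 persons served and 15 providers/administrators. The provider group may include judicial, treatment and community roles.

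**The concern.** Comparing item means between two groups presupposes that both answered the same item, on the same response scale, about the same thing. As described, the two surveys are adapted from different published tools and written for different respondents, and the article mentions no shared items and no equating. A gap could then reflect how the questions are worded, how responses are scored or what is being rated, and not a difference in view. Agreement could equally hide a real difference.

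The result would be used. The Methods section gives quantitative and qualitative data equal weight. Survey responses enter a joint display whose approach is said to show where participants' responses converge or diverge. Summaries of Aim 1 data then go to the advisory board during toolkit development. In a study about equity, a statement that clients and providers see the program's cultural competency differently, or alike, is likely to be taken as a substantive finding.

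**Working it through.** The article gives no scale range, standard deviation, effect size, significance level or power for this contrast, so there is no figure to reproduce. The check is mainly textual.

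**Step 1: set the two surveys side by side.**

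| Feature | Persons served | Providers/administrators |
|---|---|---|
| Source tool | Iowa Client Form, adapted | AUCD organizational assessment, adapted |
| Rated | MISSION-CJ and drug court providers, as clients see them | An organization (which one is not stated), and the respondent's own competency |
| Response scale | Not stated | Not stated |
| Items shared with the other survey | None described | None described |

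**Step 2: ask what the mean difference contains.** Write D for the difference between the group means:

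D = (difference in perception) + (difference due to item content) + (difference due to scale, if the scales differ) + (difference due to referent, if the referents differ).

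The source tools differ, so the second term cannot be assumed to be zero. The third and fourth are unknown. Only D is observed, so the first term cannot be isolated. A larger sample would not help, because the extra terms are bias and not sampling error.

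**Step 3: ask whether the overlap helps.** The client form is described as covering organizational culture, and the provider survey has an organizational section. The constructs are therefore related. That supports looking at the two by domain, but it does not support subtracting one mean from the other. The provider self-assessment concerns the respondent and not the program, so it has no counterpart in the client form as described.

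**Step 4: illustrate the sensitivity, on assumptions only.** None of the inputs below is in the article except the 15 per group.

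- *Scale alone.* Suppose one form ran 1–5 and the other 1–4, and both groups stood at 75% of the range. The means would be 1 + 0.75 × (5 − 1) = 4.00 and 1 + 0.75 × (4 − 1) = 3.25, which is 0.75 points apart with no true difference. If both forms use the same scale, this part is zero.
- *Any instrument-only offset d, in SD units.* Suppose also a two-sided test at 0.05 with a normal approximation. The standard error is √(2/15) = 0.365, and the chance of declaring a difference when perceptions are equal is Φ(d/0.365 − 1.96) + Φ(−d/0.365 − 1.96).

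| Assumed offset d (SD) | Chance of declaring a difference |
|---|---|
| 0 | 0.050 |
| 0.25 | 0.105 |
| 0.50 | 0.278 |
| 0.75 | 0.537 |
| 1.00 | 0.782 |

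The range runs from no harm to a false difference in most repetitions. The article does not say where in this range the study would lie, nor that a test will be run.

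**The case against.** The strongest reply has four parts.

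1. *The questionnaires are not shown.* Both tools are adapted, so some items may already have been aligned, and the plan itself labels the provider responses as ratings of the program. This is possible, and it limits how firmly non-comparability can be asserted. But the article states both the instruments and the comparison, and as stated they do not fit. If items were aligned, one sentence would settle the matter.

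2. *A reader might infer that providers rate their own separate agencies and so cannot be rating the program.* The article does not say so. It leaves the organization unnamed, and providers qualify by having served people in the MISSION-CJ programs at the study courts, so a program referent is plausible. What stands is that the referent is not fixed, and that self-assessment items do not rate the program.

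3. *A reader might infer that this is the only quantitative contrast planned.* It is not. The other grouping factors in the Aim 1 plan can mostly be compared within one instrument. In Aim 2, both groups rate the same statements on the same 0–5 scales. Those comparisons are not affected.

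4. *Little depends on it.* The survey analysis is descriptive and small. The Aim 1 deliverable is a list of barriers and facilitators, the Aim 2 statements come from the interviews, and no decision rule uses this contrast. This is correct and lowers the severity. It does not make the comparison interpretable.

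**Conclusion.** The point holds as a moderate issue. The example contrast compares means from two differently sourced instruments, so neither a difference nor its absence can be read as a perception gap between persons served and providers. The conclusion rests on the article's description of the surveys and on no alignment of items having been done beyond what is described.

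The size of any artefact cannot be computed from the article. A reader might take the 0.75-point or 54% figures as estimates for this study, but they follow from assumed scales, an assumed offset and an assumed test. Nor is the bias without limit: on a bounded rating scale it cannot exceed the scale's range. A reader might also infer that the toolkit is at risk. The documents support only that the result reaches the joint display and that Aim 1 summaries reach the advisory board. No aim's deliverable depends on it.

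**What to change.** Restrict the persons-served versus provider mean comparison to items that have the same wording apart from the respondent's viewpoint, the same response scale and the same stated referent (the MISSION-CJ/drug court program) in both surveys.

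- **If the surveys are not yet fielded:** add a short parallel block to both, for example 5–8 client-form items reworded for providers, and run the contrast on that block only. The cost, by this review's estimate, is one or two minutes on a 10–15 minute survey, a minor ethics amendment and one sentence in the analytic plan. The reworded block would be new and without established measurement properties, so it should be reported item by item.
- **If they are already fielded:** use any items that happen to match. If there are none, report each instrument within its own group and place the results by domain in the planned joint display, with no between-group mean difference. This costs only a change of wording.
- **In either case:** keep provider self-assessment items out of the contrast, and state which organization the provider items refer to.

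Comparisons within one instrument, and the Aim 2 rating comparison, need no change on this account.

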#### Methods/Design

Participants: Thirty persons served and 30 providers/administrators will be invited to participate in a concept mapping activity. Persons served and provider/administer eligibility criteria will be the same as outlined in Aim 1.

Procedures: Concept mapping is a mixed-methods approach to engage community members and providers in the community-based participatory research process [48]. Concept mapping has been effectively used to bring together diverse groups of community members and providers to expeditiously create an interpretable conceptual framework that can serve as a foundation for implementation planning. Concept mapping generates group consensus on key ideas and supports systems thinking by eliciting individual experiences to identify group conceptualization of an issue. It equalizes or lessens power differentials among participants by giving individuals equal voice and choice and engages persons served and providers as both study participants and collaborative decision-makers. Concept mapping tasks such as sorting and ranking (described below) are done individually and anonymously, so everyone gets an anonymous vote on the final conceptual naming and grouping of clusters. Since statistical procedures analyze the sorting and rating data, people do not need to discuss, defend, or develop consensus with other participants and no one person holds the decision-making power.

The concept mapping process has qualitative and quantitative components that can be conducted online, face to face (via phone or video conferencing), or in combination. The qualitative elements are **
*brainstorming ideas*
** from a prepared focus question, **
*structuring the ideas*
** by sorting them into thematic groups based on their perceived similarity and then rating them on importance and feasibility, and **
*analyzing and interpreting*
** the concept maps generated. The quantitative elements are rating the qualitative statements generated and creating different visual maps to convey key concepts. Typically, concept mapping is organized into four structured and sequenced activities: (1) brainstorming, (2) sorting, (3) rating, and (4) data interpretation.

It is important to note that this sequence does have the potential for participant burden [49]. Therefore, the concept mapping sequence in this study will be modified such that statements will be extracted from our Aim 1 qualitative interviews; sorting and rating will follow the typical concept mapping sequence; and interpretation of the concept maps will be done by an advisory board. We considered traditional concept mapping, but due to concerns of participant burden, we opted to use this adapted version which has been successfully tested by others [50]. The traditional concept mapping methodology comprises generation of ideas (statements/items) through focus group brainstorming guided by a study-specific prompt or focus question. Instead, the generation of ideas will be synthesized from the Aim 1 individual qualitative interviews. The interviews will include prompts or focus questions such as “List key strategies to ensure MISSION-CJ is reaching and benefitting all people in Drug Court”; “To eliminate disparities and achieve health equity in the treatment of COD within Drug Courts, programs should…”; “Thinking as broadly as possible, what are some strategies to ensure MISSION-CJ is reaching and benefitting people of color within the Drug Court?; and “What are the most impactful and feasible strategies to improve MISSION-CJ services for Black/African American and/or Hispanic/Latino people in Drug Court?” We will fine-tune these questions with our advisory board and pilot test the question with at least one person served and one provider.

Study participants will be asked to identify and prioritize actionable implementation activities to address barriers to equitable MISSION-CJ implementation in DTC identified in Aim 1. Concept mapping is usually an individual virtual activity. To account for technology access, literacy, and comfortability, participants will be given the options to complete the activity virtually, in-person, or by video conference. If participants are interested in completing the activity virtually, they will be provided with computer access and support as needed. The same recruitment and screening strategy described in Aim 1 will be utilized, but the study will be expanded to additional DTCs to capture additional diversity of community and provider perspectives across different DTCs in the state. Our planned sample size is slightly higher than the recommended sample size for concept mapping (*n* ≥ 15 per group) [51] to ensure we can make meaningful comparisons between persons served versus providers/administrators.

Those who agree to participate virtually will be sent a link to the online platform in either English or Spanish. The site will be available to participants for a 1-month period. On the site, participants will provide brief demographic information. Concept mapping will include a sequential process with the following steps. First, participants will view and read a list of implementation strategies synthesized from Aim 1. For the sorting task, participants will be instructed to sort the strategy statements into categories that make sense to them and to generate a label for each category they created. Next, for the rating task, all participants will be asked to rate the importance of each strategy statement on a scale ranging from 0 (not important at all) to 5 (extremely important) based on the impact each strategy would have on the equitable implementation of MISSION-CJ. All participants will then be asked to rate each strategy statement on its feasibility using the scale 0 (not feasible at all) to 5 (extremely feasible).

If the participant elects to complete concept mapping in-person, an interviewer will meet with them and guide them through the concept mapping activity on a study laptop in person. The interviewer will walk them through the steps outlined above to elicit and record participant responses in the Concept System® groupwisdom™ platform. Upon completion, participants will receive a $50 gift card. Concept mapping has been conducted successfully with similar participant populations [52].

Analyses Plan: The Concept System® groupwisdom™ [53] will be used to conduct the analyses. The software uses multidimensional scaling and hierarchical cluster analysis to interpret sorting and rating data and to produce visual representations of the data (e.g., maps). Hierarchical cluster analysis, using input from multidimensional scaling, mathematically groups each statement into adjustable cluster solutions, based on how participants rated and sorted the data. Each cluster represents a unique theme on the resulting map. Descriptive statistics for the importance and feasibility ratings will be calculated. Each implementation strategy’s importance and feasibility score will be plotted on a graph. The PI will present results to the advisory board to understand and interpret concept mapping results.

### 
Aim 3: Develop a Health Equity-Informed MISSION-CJ Implementation Toolkit via an Iterative Development Process with Our Advisory Board

#### Methods/Design

Procedures: Data summaries from Aims 1 and 2 will be reviewed with our advisory board who will help interpret the findings to inform development of a toolkit to advance equitable implementation of MISSION-CJ in DTCs. The PI will facilitate discussion and gather consensus for modifications.

Toolkit Development: The study team will draft and refine toolkit content with iterative feedback from the advisory board. Each of the newly developed components will be beta-tested with the board and their feedback will inform the final version of the toolkit to be used in a larger trial. The board will provide commentary on what they like, dislike, and changes for improvement. For example, if implementation strategies such as “strategies to increase ongoing person served feedback on the MISSION-CJ implementation; identifying/preparing a provider and/or person served program champion, or culturally tailoring MISSION-CJ components” are suggested as important and feasible strategies to advance equitable implementation in Aims 1 and 2, the advisory board will review toolkit sections related to these strategies (e.g., sample focus group instructions and questions to be used by programs to solicit participant/family feedback). Utilizing the nominal group technique, we will present a toolkit section (e.g., strategies to identify and prepare graduates of color to serve as program champions) then (1) ask members to silently generate ideas about how best to enhance it, (2) gather round-robin feedback from group members to record each idea, (3) discuss each recorded idea for clarification and evaluation, and then (4) conduct individual and anonymous polling to identify priorities for further refinement. The final toolkit will be assessed by board members via the Acceptability of Intervention Measure, Intervention Appropriateness Measure, and Feasibility of Intervention Measure [55], four-item measures to determine to what extent the toolkit is acceptable (e.g., Is it agreeable, palatable, satisfactory?), appropriate (e.g. Is it relevant or a fit?), and feasible (e.g., Can it be successfully used in DTCs?).

The toolkit will help MISSION-CJ end users (providers, courts, and systems) use strategies to close gaps in behavioral healthcare outcomes that result from multilevel and inequitable policies and practices. The toolkit will include:Supporting evidence on why both uptake and equity are important;Tactical and practical steps to equitably implement evidence-based COD programming in DTC;Strategies to address issues arising from variation and obstacles within settings;Strategies to evaluate and enhance equitable implementation of evidence-based COD programming in DTC;Suggested training to ensure staff and leadership share a common understanding of the complexities of inequities and have the skills to advance health equity.

